### Randomization and Blinding

Computer randomization will be performed by the team’s biostatistician, using a permuted block randomization technique stratified by baseline sleep medication use (yes or no) [36]. Other personnel (except for therapists, supervisor, and project coordinator) will be blinded to randomization.

### Procedures

#### Screening

A sleep psychologist (principal investigator [name]) will diagnose insomnia and make referrals for other suspected sleep disorders (eg, apnea). Screening will be carried out in four stages:

Stage 1: brief screener (15 minutes). The project coordinator will (1) conduct a brief structured interview to address the inclusion and exclusion criteria and establish a probable insomnia diagnosis and (2) administer the Montreal Cognitive Assessment (CG must score >25, a cutoff chosen to maintain consistency with our prior clinical trial).Stage 2: clinical interview (50 minutes). The assessor will (1) conduct a semistructured sleep and psychiatric interview and (2) facilitate and assist with web-based baseline questionnaire completion.Stage 3: apnea testing (1 overnight session). This consists of 1 night of at-home sleep testing using disposable WatchPAT One devices (Itamar Medical Ltd) to rule out sleep disorders other than insomnia (ie, apnea). The assessor will instruct CGs on how to use WatchPAT One devices in their own homes so that the CGs can sleep in their own beds. Referrals will be made for those disqualified. The WatchPAT One (a wrist-worn device with 2 finger sensors) measures peripheral arterial tone, oximetry, actigraphy, HR, body position, and snoring.Stage 4: sleep diary confirmation of insomnia (5 minutes per day). Electronic baseline diaries will confirm insomnia diagnosis and must show >30 minutes of sleep onset latency or wake after sleep onset on ≥3 nights over 7 days. Diaries will be collected electronically through Qualtrics software with personal web-enabled devices or (if needed) study-provided devices and internet service.

#### Interventions

Both arms (NiteCAPP CARES and NiteCAPP SHARES) include 4 web-based sessions and 4 bimonthly, 20-minute boosters (Figure 2) with a therapist moderator (predoctoral graduate students in an American Psychological Association–accredited psychology program at the University of Missouri). Details of the development of NiteCAPP have been published and are available [7]. Each session is completed individually by CGs (with persons with dementia to the extent able) in a single sitting (<45 minutes). Each session should be completed in 7 days, with the next session released only after the previous one is completed. All procedures will be conducted at participants’ homes. Session content details for NiteCAPP CARES and NiteCAPP SHARES are provided in Textboxes 1 and 2, respectively.

Both interventions will be dyadic, and CGs will work with persons with dementia to implement behavioral strategies similar to those used by McCrae et al [10] and McCurry et al [12]. Active participation of persons with dementia is a goal but may be limited because of dementia symptoms. Behavioral strategies for persons with dementia will be tailored based on baseline assessment (use of actigraphy in persons with dementia, nighttime behaviors, and dementia severity and other questionnaires). To provide a guided therapy approach, trained moderators (psychology doctoral students) will (1) monitor adherence and progress (log-in details and log completion), (2) provide weekly email feedback on sleep patterns and progress, (3) answer questions within 24 hours through a web-embedded message forum, and (4) provide bimonthly boosters (discuss maintenance and troubleshoot problems).

**Figure 2 figure2:**
[figure not shown]
Session and booster timeline. The randomization numbers refer to dyads (ie, caregivers and their coresiding persons with dementia). B: booster session; F6: 6-month follow-up; F12: 12-month follow-up; NiteCAPP CARES: cognitive behavioral therapy for insomnia; NiteCAPP SHARES: active web-based sleep hygiene and related education control.

Session content for NiteCAPP CARES.
**1. Sleep hygiene, sleep education, and stimulus control**
Sleep hygiene will be taught, and participants are instructed to adhere to the following rules (the goal of sleep hygiene is to eliminate sleep-interfering behaviors):avoid caffeine after noonwithin 2 hours of going to bed, avoid exercise and heavy mealswithin 1 hour of bedtime, avoid screen timeuse the bed for sleeping only
**2. Sleep compression, relaxation, and problem solving**
The therapist moderator and caregiver and person with dementia will work together to create a sleep prescription and set regular bed and wake times consistent with the prescription. Caregiver and person with dementia will be instructed to practice relaxation techniques. Caregiver will be provided suggestions on how to solve the challenges associated with caregiving for a person with dementia.
**3. Coping and stress management and cognitive therapy**
Sleep prescription for caregiver and person with dementia will be updated as appropriate. Coping and stress management techniques will be taught. Caregiver and person with dementia will be taught how to identify maladaptive thoughts and replace them with balanced thoughts.
**4. Review and education and plan for maintenance of behavior change**
Sleep prescription for caregiver and person with dementia will be updated as appropriate. Caregiver and person with dementia will be provided information on how to maintain sleep changes.
**5. Booster sessions**
In this brief (approximately 20 minutes) telephone session, techniques from sessions 1 to 4 will be reviewed. The therapist moderator will encourage continued practice of techniques and assist in troubleshooting of problems.

Session content for NiteCAPP SHARES.
**1. Expanded sleep education and sleep hygiene**
Participants are provided sleep education regarding sleep and the brain, mood, behavior, health, and weight. Sleep hygiene will be taught and participants are instructed to adhere to the following rules (the goal of sleep hygiene is to eliminate sleep-interfering behaviors):avoid caffeine after noonwithin 2 hours of going to bed, avoid exercise and heavy mealswithin 1 hour of bedtime, avoid screen timeuse the bed for sleeping only
**2. Insomnia education and sleep hygiene support**
Participants are provided education on sleep stages and cycles, sleep disorders, and safety precautions regarding sleep.
**3. Targeted sleep education and sleep in dementia**
Participants are provided targeted sleep education and education about sleep in dementia.
**4. Review and education and plan for maintenance of behavior change**
Sleep prescription for caregiver and person with dementia will be updated as appropriate. Caregiver and person with dementia will be provided information on how to maintain sleep changes.
**5. Booster sessions**
In this brief (approximately 20 minutes) telephone session, techniques from sessions 1 to 4 will be reviewed. The therapist moderator will encourage continued practice of techniques and assist in troubleshooting of problems.

#### Treatment Integrity

The 3-step method formulated by Lichstein [37] will be used to measure treatment integrity.

##### Step 1: Treatment Delivery and Training

Moderators use web-based manuals. Practice begins with mock web-based sessions (ie, moderator and patient interactions), followed by web-based sessions with volunteers. The principal investigator ([name]), a licensed psychologist who is board certified in behavioral sleep medicine, will score all training sessions. Training lasts approximately 8 weeks until the moderators obtain mastery (scoring 100 on each session’s *Moderation Score Sheet*). All moderator-provided feedback will be delivered through email. Transcripts of moderator and participant interactions will be stored, and 25% will be scored by the consultant (a licensed psychologist). A senior consultant (a licensed psychologist) will double score the initial 10 sessions and 10 boosters and then 10% of the remaining sessions for reliability. Consultants will inform the principal investigator ([name]) of scores <95% for supervisory and training purposes. The principal investigator ([name]) will review 25% and the moderators will review 25% of each other’s sessions for ongoing training and supervision. Only consultant reviews will be used to assess fidelity.

##### Step 2: Treatment Receipt

Each week, participants will be emailed a link to their assigned session. Automatic prompts and moderator emails will be used to encourage session completion. To ensure treatment comprehension, participants will be encouraged to ask questions using the embedded communication portal. Moderators will monitor and respond within 24 hours to messages sent through the system. Web-based materials will describe and reinforce treatment content. Time spent viewing web-based sessions will be monitored and recorded. Participants will complete a brief web-based quiz at the end of session 2.

##### Step 3: Treatment Enactment

To ensure that assignments are completed (eg, relaxation session completed and instructions followed), web-based materials contain simple written instructions. Participants will maintain daily electronic diaries and logs. Participants will complete a patient satisfaction and experience survey at the posttreatment and follow-up assessments. Reasons for withdrawal will be assessed using a withdrawal questionnaire.

#### Treatment Credibility and Expectancy

At the end of session 2, participants will complete a treatment credibility questionnaire. The treatment credibility questionnaire is a 4-item scale that assesses the participant’s reaction to therapist and treatment efficacy, and participants provide ratings of 1 (strongly disagree) to 10 (strongly agree). Higher scores represent better treatment credibility.

### Outcomes

A summary of study outcome measures is provided in Table 1 and schedules of outcome and process measures are provided in Tables 2 and 3.

**Table 1 table1:** Outcome measures.

Outcome category and measure			Details

	**Utility and treatment satisfaction**		
		Internet Intervention Utility Questionnaire [38]	This is a 16-item measure designed to assess usability, likeability, usefulness, understandability, and convenience of an internet intervention using a 5-point Likert scale, ranging from 0 (not at all) to 4 (very); 2 additional open-ended questions ask about the most and least helpful aspects of the program.
		Satisfaction Survey	This is a 9-item measure designed to provide feedback on the study, including its structure, assessments, scheduling, working with study staff, and the usability of the intervention platforms using a 10-point Likert scale, ranging from 1 (strongly disagree) to 10 (strongly agree), and open-ended questions.
**Aim 2: primary and mechanistic caregiver outcomes**			
	**Sleep**		
		Daily sleep diaries	Daily electronic diaries assess caregiver sleep onset latency (lights out until sleep onset), wake after sleep onset, and sleep efficiency (total sleep time/time in bed × 100%).
		Insomnia Severity Index [39]	This is a 7-item measure designed to assess the nature, severity, and impact of insomnia using a 5-point Likert scale, ranging from 0 (no problem) to 4 (very severe problem).
	**Arousal**		
		Peripheral arousal: HRV^a^	HRV will be assessed using a Holter monitor during an established stress reactivity protocol. Participants will be seated at rest and undergo Holter monitoring procedures: (1) 5 minutes, baseline; (2) 30 seconds, vibrotactile stimuli (Conair WM200X) at 80 Hz oscillations applied to left hand; (3) 3 minutes, recovery; (4) 30 seconds, vibrotactile stimuli applied to right hand; (5) 3 minutes, recovery; (6) cold pressor stimulation to right hand (place hand at bottom of bowl of ice water calibrated to 4 °C); (7) 3 minutes, recovery; and (8) cold pressor stimulation to left hand. Time and spectral analysis of short-term HRV during baseline, vibration, and cold pressor stimuli will be conducted using Pathfinder software (Spacelabs Healthcare). Time (reflects beat-to-beat variability: RMSSD,^b^ pNN50^c^) and frequency (reflects underlying HR^d^ rhythms: high, 0.15-0.4 Hz; low, 0.04-0.15 Hz; very low, <0.04 Hz, and LF^e^:HF^f^ ratio] domains will be examined. Vibration and cold pressor hand placement order will be counterbalanced every 10 participants to account for order effects.
		Chronic stress: hair cortisol	With permission, research staff will cut hair strands as close as possible to scalp (forearm if needed [40]; minimum 50 mg of hair per sample).
		Perceived Stress Scale [41]	This is a 10-item measure designed to assess past-month stress levels in response to everyday situations using a 4-point Likert scale ranging from 0 (never) to 4 (very often).
		Kingston Caregiver Stress Scale [42]	This is a 10-item measure designed to assess three categories—caregiving, family, and financial issues—using a 5-point Likert scale ranging from 1 (feeling fine or no stress) to 5 (extreme stress).
		Dysfunctional Beliefs and Attitudes about Sleep [43]	This is a 30-item measure designed to assess dysfunctional beliefs and attitudes about sleep using a 10-point Likert scale ranging from 0 (strongly disagree) to 10 (strongly agree).
**Aim 3: secondary health-related caregiver outcomes**			
	**Health and mood**		
		SF-36^g^ [44]	This is a 36-item measure designed to assess quality of life using a 5-point Likert scale ranging from 1 (poor) to 5 (excellent).
		Beck Depression Inventory [45]	This is a 21-item measure designed to assess depressive symptomatology using a 4-point Likert scale ranging from 0 (absence of symptoms) to 3 (severe).
		State-Trait Anxiety Inventory [46]	This is a 20-item measure designed to assess anxiety using a 4-point Likert scale ranging from 1 (not at all) to 4 (very much so).
	**Burden**		
		Zarit Burden Scale [47]	This is a 22-item measure designed to assess burden using a 5-point Likert scale ranging from 0 (never) to 4 (nearly always).
		Quality of life of caregiver of patient with dementia [48]	This is a 20-item measure designed to assess how caregiver quality of life changes after beginning caregiving using yes or no questions and a 10-point sliding scale ranging from 0 (easy) to 10 (hard).
	**Cognition**		
		Daily Joggle battery [49]	Web-based battery designed to assess daily cognitive performance in multiple domains, including processing speed and attention (psychomotor vigilance and digit symbol substitution tasks), visuospatial ability and memory (visual object learning and line orientation tasks), verbal learning and memory (auditory verbal learning task), and executive functioning and working memory (abstract matching and n-back tasks).
		NIH Toolbox for Assessment of Neurological and Behavioral Function [50]	Computerized measure designed to assess cognitive performance in multiple domains, including processing speed and attention (pattern comparison task), visuospatial ability and memory (picture sequence learning task), verbal learning and memory (auditory verbal learning task), and executive functioning and working memory (dimensional card sort and a flanker inhibition tasks).
		Cognitive Failures Questionnaire [51]	This is a 25-item measure designed to assess an individual’s perception of their own daily cognitive failures (eg, absentmindedness and memory errors) using a 5-point Likert scale ranging from 0 (never) to 4 (very often).
	**Inflammation**		
		Blood-based biomarkers	High-sensitivity CRP^h^ and IL-6^i^. Plasma proteins are digested with trypsin, and peptides specific for CRP and IL6 are quantified using multiple reaction monitoring mass spectrometry.
	**Neurodegeneration**		
		Blood-based biomarkers	Aβ^j^40/42, tau, p-tau^k^-181, and p-tau-217. Plasma is extracted (Aβ40/42), or plasma proteins are digested with trypsin, and peptides are quantified using multiple reaction monitoring mass spectrometry.
**Aim 4: persons with dementia: secondary outcome (sleep change in persons with dementia)**			
	**Actigraphy**		Actiwatch 2 (Philips Respironics) is a watch-like device that will be worn 24/7 during each 1-week assessment to monitor light and gross motor activity. Data will be analyzed using 30-second epochs and a validated algorithm (Actiware-Sleep version 3.3; Mini Mitter Co, Inc) to estimate total wake time.
**Exploratory aim: moderators**			
	**Demographics**		
		Demographics	Socioeconomic status, race and ethnicity, education level, marital status, financial strain, residence, menopause symptoms, medications, comorbidities, distance (miles) to the nearest provider, and rurality (Rurality Index [52]).
	**Interpersonal**		
		Patient-Caregiver Functional Unit Scale [53]	This is a 43-item measure designed to assess how much assistance the person with dementia needs and caregiver feelings about helping using yes or no questions and 2 types of Likert scales: a 3-point scale ranging from 0 (without help) to 2 (completely unable) and a 4-point scale ranging from 0 (no) to 3 (both physically and emotionally difficult).
	**Shared lifestyle**		
		Godin-Shephard Leisure-Time Physical Activity Questionnaire [54]	This is a 3-item measure designed to assess how many times per week an individual engages in mild, moderate, or strenuous activity and asks the number of times per week the items were accomplished.
		Fruit and vegetable servings	Amount of fruit and vegetable servings per day
	**Respite and assistance**		
		Respite	Amount and type of respite
		Assistance	Assistance provided by secondary informal caregivers (number, relationship, hours: face-to-face vs other).
	**Dementia severity of persons with dementia**		
		Dementia Severity Rating Scale [55]	This is an 11-item measure designed to assess severity of functional and cognitive decline in patients with Alzheimer disease using various Likert scales.
	**Nighttime behaviors of persons with dementia**		
		Neuropsychology Inventory Nighttime Behavior Scale [56]	This is an 8-item measure designed to assess frequency and severity of detrimental sleep behaviors, such as wandering, in the dementia patient using yes or no questions.

^a^HRV: heart rate variability.

^b^RMSSD: root mean square of successive RR interval differences. RR interval is the time between 2 detected heartbeats, calculated for every QRS event.

^c^pNN50: The proportion of NN50 divided by the total number of NN (R-R) intervals. NN50 is the number of times successive heartbeat intervals exceed 50 ms. RR interval is the time between 2 detected heartbeats, calculated for every QRS event. NN interval is the time (normalized) between 2 detected heartbeats, calculated for every QRS event.

^d^HR: heart rate.

^e^LF: low frequency.

^f^HF: high frequency.

^g^SF-36: Short Form-36 Health Survey Questionnaire.

^h^CRP: C-reactive protein.

^i^IL-6: interleukin-6.

^j^Aβ: plasma amyloid beta.

^k^p-tau: phosphorylated tau.

**Table 2 table2:** Schedule of outcome measures.

	Baseline	Treatment	After treatment	Boosters	6-month follow-up	12-month follow-up
Assessment period, weeks	1	4	1	1	1	1
Screening, apnea testing, consent and assent, and demographics	✓					
HRV,^a^ ISI,^b^ PSS,^c^ KCGSS,^d^ inflammation and neurodegeneration biomarkers, cortisol, actigraphy, SF-36,^e^ BDI,^f^ STAI,^g^ DBS,^h^ ZBS,^i^ QoL,^j^ daily Joggle battery, NIH Toolbox for Assessment of Neurological and Behavioral Function, CFQ,^k^ P-CG FUS,^l^ G-S L-T PAQ,^m^ fruit and vegetable servings per day, respite, secondary CG^n^ outcomes, DSRS,^o^ NPI,^p^ and NBS^q^	✓		✓		✓	✓
Electronic daily diaries	✓	✓	✓	✓	✓	✓

^a^HRV: heart rate variability.

^b^ISI: Insomnia Severity Index.

^c^PSS: Perceived Stress Scale.

^d^KCGSS: Kingston Caregiver Stress Scale.

^e^SF-36: Short Form-36 Health Survey Questionnaire.

^f^BDI: Beck Depression Inventory.

^g^STAI: State-Trait Anxiety Inventory.

^h^DBS: Dysfunctional Beliefs about Sleep.

^i^ZBS: Zarit Burden Scale.

^j^QoL: Quality of life of caregiver of patient with dementia.

^k^CFQ: Cognitive Failures Questionnaire.

^l^P-CG FUS: Patient-Caregiver Functional Unit Scale.

^m^G-S L-T PAQ: Godin-Shephard Leisure-Time Physical Activity Questionnaire.

^n^CG: caregiver.

^o^DSRS: Dementia Severity Rating Scale.

^p^NPI: Neuropsychological Inventory.

^q^NBS: Nighttime Behavior Scale.

**Table 3 table3:** Schedule of process measures.

	Baseline	Treatment	After treatment	Boosters	6-month follow-up	12-month follow-up
Assessment period (weeks)	1	4	1	1	1	1
Treatment integrity: delivery and receipt and enactment		✓		✓		
Treatment credibility: quiz and improvement expectancy		✓	✓		✓	✓
Sleep knowledge and working alliance		✓	✓	✓	✓	✓

### Study Timeline

The study timeline is provided in Table 4.

**Table 4 table4:** Study timeline.

	Project year										
	1		2		3		4			5	
	First half	Second half	First half	Second half	First half	Second half	First half	Second half	First half		Second half
Develop manual of operating procedures, register with ClinicalTrials.gov, publish trial protocol, and train moderators and assessors	✓										
Recruit, collect baseline measurements, and deliver treatment		✓	✓	✓	✓	✓	✓				
Collect assessment after treatment		✓	✓	✓	✓	✓	✓	✓			
Collect 6- and 12-month follow-up assessments			✓	✓	✓	✓	✓	✓	✓		
Offer and provide NiteCAPP CARES^a^ to NiteCAPP SHARES^b^ participants				✓	✓	✓	✓	✓	✓		✓
Final data analysis and dissemination (continues after grant ends) and final report									✓		✓

^a^NiteCAPP CARES: cognitive behavioral therapy for insomnia.

^b^NiteCAPP SHARES: active web-based sleep hygiene and related education control.

### Analytical Approach

#### Power Analysis

Power will be simulated using SAS 9.4 statistical software (SAS Institute Inc) using a generalized estimating equations (GEE) design (clusters are individuals measured over 4 time points) with an autoregressive working correlation structure (correlation decreases as time point distance increases, *ρ*=0.5, 1 million Monte Carlo integrations simulated) [57]. The approach described by Schluchter [58] will fit GEE models with and without mediator to estimate mediated effect (exploratory aim). Sample size of 80 is powered (>.80) to detect small to large Cohen *d* mediation effects. Given an anticipated dropout rate of 15% to 20%, we will recruit a total sample of 120.

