**Methods:**

Dyads (n=100) consisting of caregivers with chronic insomnia and their coresiding persons with dementia will be recruited from Columbia and surrounding areas in Missouri, United States. Participant dyads will be randomized to 4 weeks (plus 4 bimonthly booster sessions) of NiteCAPP CARES or a web-based sleep hygiene control (NiteCAPP SHARES). Participants will be assessed at baseline, after treatment, and 6- and 12-month follow-ups. The following assessments will be completed by caregivers: 1 week of actigraphy and daily diaries measuring sleep, Insomnia Severity Index, arousal (heart rate variability), inflammation (blood-derived biomarkers: interleukin-6 and C-reactive protein), neurodegeneration (blood-derived biomarkers: plasma amyloid beta [Aβ40 and Aβ42], total tau, and phosphorylated tau [p-tau181 and p-tau217]), cognition (Joggle battery, NIH Toolbox for Assessment of Neurological and Behavioral Function, and Cognitive Failures Questionnaire), stress and burden, health, and mood (depression and anxiety). Persons with dementia will complete 1 week of actigraphy at each time point.

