## Methods

### Trial Design and Study Setting

Dyads (n=100) consisting of CGs with chronic insomnia and their coresiding persons with dementia will be recruited from Columbia and surrounding areas in Missouri, United States, and randomized to 4 sessions of NiteCAPP CARES or NiteCAPP SHARES. The groups will receive bimonthly boosters. Baseline and posttreatment assessments as well as 6-month and 12-month follow-ups will measure sleep, arousal, biomarkers of inflammation and neurodegeneration, health, mood, burden, and cognition.

Graduate therapists and assessors will obtain written informed consent from CGs and persons with dementia, if possible. If the person with dementia is unable to consent (determined by consultation with the first author [[name]]), a legally authorized representative must sign a consent form on their behalf. If the person with dementia becomes unable to provide consent during the course of the study, the legally authorized representative will be asked to reconsent on behalf of the care recipient. Dyads in both groups will receive US $125 at baseline, US $150 after treatment, US $175 at 6-month follow-up, and US $200 at 12-month follow-up, as well as treatment at no cost. NiteCAPP SHARES participants will be offered NiteCAPP CARES at no cost after the study.

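### The Power Analysis recruits 120, but the design says 100 dyads and the paragraph's own inputs give 95 to 100; the *small* mediation effect in its power claim is undefined

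*Protocol article*

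**What the plan says.** The protocol article gives the enrolment figure in three places.

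- Abstract, Methods: "Dyads (n=100) consisting of caregivers with chronic insomnia and their coresiding persons with dementia will be recruited".
- Trial Design and Study Setting: "Dyads (n=100) consisting of CGs with chronic insomnia and their coresiding persons with dementia will be recruited". The same sentence goes on to randomise these dyads to the two arms.
- Power Analysis: "Given an anticipated dropout rate of 15% to 20%, we will recruit a total sample of 120". No unit is attached to this total.

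The only power statement is in the Power Analysis: "Sample size of 80 is powered (>.80) to detect small to large Cohen" *d* mediation effects. The model is a GEE in which "clusters are individuals measured over 4 time points", with an autoregressive working correlation of 0.5. Mediation is to be estimated by fitting models with and without the mediator, and the paragraph assigns this to the exploratory aim. It gives no alpha, no numeric effect size and no path coefficients. The text shown gives no allocation ratio.

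**The concern.** Both figures are described as numbers to be recruited, and they differ by 20. The recruitment total decides when enrolment is complete. With two published totals, stopping at 100 can be called a shortfall and continuing to 120 an extension. The derivation is also in doubt, because the paragraph offers dropout as the only reason for 120 and the stated dropout does not lead there.

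The power sentence raises a lesser question. Power above 0.80 for a small mediated effect with 80 participants is a strong claim, and whether it is attainable depends on what *small* refers to. The paragraph leaves that open.

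**Working it through.** **Recruitment total**

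Inputs from the Power Analysis: 80 analysable, dropout 15% to 20%, stated result 120.

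1. Usual inflation, N/(1 − dropout): 80/0.85 = 94.1, so 95; 80/0.80 = 100. The stated 120 is not reproduced.
2. Simple mark-up, N × (1 + dropout): 80 × 1.15 = 92; 80 × 1.20 = 96. Again not 120.
3. Dropout implied by 120 and 80: 1 − 80/120 = 33%.
4. Analysable number if 120 are recruited: 120 × 0.80 = 96; 120 × 0.85 = 102.
5. Analysable number if 100 are recruited: 100 × 0.80 = 80; 100 × 0.85 = 85. This agrees with the 80 in the power statement.
6. One way to obtain 120 is from a base of 100: 100 × 1.20 = 120. That would apply dropout a second time to a figure that already contains it. This is a guess at the origin; the document does not say.
7. Units do not help. 100 dyads are 100 caregivers or 200 persons, and neither is 120.

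**Power sentence**

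From the document: N = 80, four time points, autoregressive correlation 0.5. Assumptions, because the text does not give them: two-sided alpha 0.05, 1:1 allocation (40 per arm), and 0.2, 0.5 and 0.8 SD for small, medium and large.

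*Mediation, the claim actually made.* Simulation with 4,000 replicates per setting used three post-baseline visits and generalised least squares with the correlation known, which is favourable. Here *a* is the treatment-to-mediator effect and *b* the mediator-to-outcome effect. Each cell gives power by joint significance of both paths, then by the Sobel test.

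| a | b | a × b | Not baseline-adjusted | Baseline-adjusted |
|---|---|---|---|---|
| 0.2 | 0.14 | 0.028 | 13% / 4% | 16% / 5% |
| 0.2 | 0.39 | 0.078 | 21% / 19% | 24% / 21% |
| 0.2 | 0.9 | 0.18 | 22% / 22% | 25% / 25% |
| 0.5 | 0.14 | 0.07 | 47% / 25% | 51% / 30% |
| 0.8 | 0.14 | 0.112 | 58% / 48% | 60% / 52% |
| 0.5 | 0.4 | 0.20 | 82% / 79% | 89% / 87% |
| 0.8 | 0.25 | 0.20 | 97% / 95% | 97% / 96% |

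With *a* = 0.2, power stays at or below about 25% even with *b* = 0.9, because the treatment-to-mediator effect must itself be detected. With *a* = 0.2 and 120 analysed, the highest simulated figure is 34%. An indirect effect of 0.2 built on a medium or large *a* reaches 79% to 97%.

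*Direct group effect, for context only.*

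- Change from baseline to post-treatment: variance 2(1 − 0.5) = 1, so SE = √(2/40) = 0.224. Power at d = 0.2 is Φ(0.2/0.224 − 1.96) = Φ(−1.07), or 14%. The effect detectable with 80% power is (1.96 + 0.84) × 0.224 = 0.63.
- Most favourable model, a common effect over three follow-ups adjusted for baseline: SD 0.707, so SE = 0.707 × 0.224 = 0.158. Power is Φ(0.2/0.158 − 1.96) = Φ(−0.70), or 24%. The detectable effect is 2.80 × 0.158 = 0.44.

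**The case against.** On the recruitment total, one might read 120 as recruited and 100 as randomised. The Trial Design section rules this out, since its 100 dyads are both recruited and randomised. Screening loss is not available as an explanation either, because the paragraph gives only dropout. Figure 2, whose caption mentions randomisation numbers, is not shown, but no figure could make both written totals right. Nothing of this objection stands.

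On power, the objection is substantial and most of it stands.

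- A reader might infer from the 14% to 24% that the stated power is refuted. It is not: the sentence concerns mediation, and the article claims no power for direct group contrasts.
- A reader might go further and say the mediation claim is false. The document does not support that either, since an indirect effect of 0.2 with a medium or large first path comes close to or exceeds 0.80.
- Equal arms, alpha 0.05 and 0.2 for small are assumptions, not the stated design.
- The simulation tests the two paths, whereas the plan compares GEE models with and without the mediator. The simulated figures are therefore indicative and not the plan's own.
- The missing detectable effect for Aim 2 could be called an error. In a condensed article, with the full protocol and SAP not shown, it is not one.
- Weighted GEE on all randomised participants may carry more information at the post-treatment visit than 80 completers, so 0.63 is somewhat conservative.

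It would also be too much to say that the enrolment target is undefined, or that a null result will be taken to exclude small effects. The target is stated inconsistently, and nothing in the article proposes that interpretation.

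**Conclusion.** The recruitment figure of 120 is wrong as written. It contradicts the 100 dyads in the Abstract and Trial Design, and it does not follow from 80 analysable with 15% to 20% dropout, which gives 95 to 100. This needs no outside assumption and is held with high confidence.

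The power claim is unsupported in one respect, at lower confidence: *small* is not defined. Under the assumptions listed, power is at most about 25% if the treatment-to-mediator effect is 0.2. It reaches about 80% only if *small* describes an indirect effect of about 0.2 built on a medium or large treatment-to-mediator effect.

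**What to change.** 1. State one total, in dyads, in the Abstract, Trial Design and Power Analysis. Either 100 randomised, giving 80 to 85 analysable at the stated dropout, or, if 120 is the real target, 120 giving 96 to 102, with the power statement recomputed for that number. If Figure 2 carries a total, it should agree.
2. In the power sentence, give alpha, allocation and the path sizes assumed, or delete *small* from the claim.
3. Advisable but not required of a condensed article: add the effect detectable with 80% power for the Aim 2 contrast. Under the assumptions above and 80 analysable, this is about d = 0.44 (common effect over follow-up, baseline-adjusted) to 0.63 (change to post-treatment).

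Keeping 100 costs only corrected text and a less favourable description of power. Choosing 120 means 20 more dyads than the design sections state.
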